### Recruitment

Individuals will be recruited through posters on bulletin boards at all Chinese medicine centers, polyclinics, and mobile clinics under the management of Pok Oi Hospital, through social media, and by cross-referral from the Chinese medicine practitioners of these clinics. Individuals interested in participating in the study will be referred to or will self-approach Pok Oi Hospital—The Chinese University of Hong Kong Chinese Medicine Centre for Training and Research (Shatin) to undergo eligibility assessment. They will be prescreened through a telephone interview. Potential candidates for recruitment to the study will have a face-to-face interview arranged to confirm their eligibility. During the interview, investigators will explain the overall objectives and nature of the study, describe the informed consent process, and assess the candidates’ eligibility. After an individual voluntarily reviews and signs the informed consent form, information such as sex, age, height, weight, BMI, and medical history will be collected. In addition, baseline assessment of primary and secondary outcome measures will be administered. An independent staff person who is not involved in the study will thereafter randomly allocate the study participants to one of two groups. A schedule for the treatment procedure will be assigned. The study flow is shown in Fig. 1. Figure 2 presents the schedule of enrollment, interventions, and assessments.

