### Randomization and blinding

The treatment allocation into the electroacupuncture plus warm needling therapy or waitlist control groups of each eligible individual in the study will be determined by a randomization process. The random allocation to the two arms of the study will be achieved using Random Allocation Software [34] following a balanced 1:1 pattern (electroacupuncture plus warm needling therapy:waitlist control) with a block size of 10. This randomization process will be conducted by an independent staff person who is not involved in the study to guarantee concealment of the allocations. The information on the allocation list will remain strictly confidential. The allocations will be concealed and sequentially numbered; opaque, sealed envelopes will be used to contain the randomization assignments.

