#### Primary outcome measure

The primary outcome measure will be the mean change in the pain intensity of the first step (i.e., first-step pain) between the baseline and after treatment (i.e., week 4). First-step pain is the pain experienced after a long period of not bearing weight, such as upon first stepping out of bed in the morning, and is a common complaint of individuals with plantar heel pain [3, 15], measured with a 100-mm VAS. The VAS for pain is a widely used measurement of pain intensity [47–49]. It is a continuous scale ranging from 0 to 100, where 0 represents “no pain” and 100 represents the “worst imaginable pain”.

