### Statistical analysis

#### Sample size calculation

The sample size calculation will be based on the primary outcome and evaluated with the OpenEpi statistical program [58]. The sample size estimate is based on a two-arm normal design. A two-sided test with an α level of 0.05 and 80% power detects a minimally important difference of 19 mm with a standard deviation of 28 mm (first-step pain as measured by the VAS) [54]. With an assumed attrition rate of 10%, each group will require 40 individuals, which implies a total sample size of 80 individuals for the entire trial.

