#### Statistical methods and analysis

The statistical analysis will be conducted based on the intention-to-treat principle. Continuous variables will be summarized using the means and standard deviations or the means and 95% confidence intervals. Categorical variables will be summarized using counts and percentages.

The measurement data will first be tested using a normality test. For the descriptive analysis, data will be evaluated for normality and log-transformed when necessary. Two-sample *t* tests or the Wilcoxon rank-sum tests for continuous data and Pearson chi-squared tests or Fisher’s exact tests for categorical data will be conducted, depending on whether the data are normally distributed or skewed.

For the primary outcome, the paired *t* test or Wilcoxon signed-rank test will be used to perform a within-group comparison on the mean change between scores assessed before and after treatment. The two-sample *t* test or Wilcoxon rank-sum test will be used for comparisons between groups. The mean differences in other secondary outcome measures will be analyzed by following the same methodology used in the primary outcome measurement. In addition, longitudinal mixed-effects model repeated-measures tests will also be conducted to analyze the mean change in outcome measurements from the baseline to the end of the trial between the two study groups.

Analyses of data in this study will be performed using SPSS (IBM Corp, Armonk, NY, USA) and/or Stata software (StataCorp LLC, College Station, TX, USA). Multiple imputation techniques will be used to manage missing values. All tests will be two-sided, and *P* < 0.05 will be considered statistically significant.

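### The primary comparison of change in first-step pain ignores baseline VAS; adjusting for it would cost nothing and gain a modest amount of precision

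*Protocol article*

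**What the plan says.** All references are to the protocol article.

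- **Endpoint** (Primary outcome measure): "The primary outcome measure will be the mean change in the pain intensity of the first step", from baseline to week 4, on a 100-mm VAS.
- **Test** (Statistical methods and analysis): the between-group comparison is fixed as the two-sample t "test or Wilcoxon rank-sum test will be used for comparisons between groups". No covariate is named. The secondary outcomes follow the same method.
- **Further model** (same section): a longitudinal mixed-effects repeated-measures analysis is added to these tests. It is not called primary, and nothing is said about how it handles baseline.
- **Baseline data** (Recruitment): before allocation, "baseline assessment of primary and secondary outcome measures will be administered".
- **Allocation** (Randomization and blinding): 1:1 "with a block size of 10". No stratification by baseline pain is described.
- **Entry rule** (Inclusion criteria): first-step pain of at least 50 mm on the 0–100 mm scale.
- **Sample size** (Sample size calculation): at 80% power and a two-sided 5% level, the design "detects a minimally important difference of 19 mm with a standard deviation of 28 mm". The group size allows for dropout: "With an assumed attrition rate of 10%, each group will require 40 individuals".

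**The concern.** Subtracting baseline from week 4 amounts to a regression in which the baseline slope is set to 1 instead of estimated. If the true slope is below 1, the change score over-corrects a chance baseline difference between arms; if it is above 1, it under-corrects. In both cases the estimate carries avoidable noise. A model with baseline as a covariate estimates the slope. In large samples it is at least as precise, and the two methods tie only when the slope is 1.

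The trial expects about 36 evaluable patients per arm and has little power to spare above 80%. Block randomization balances numbers but not baseline pain. What is at stake is some precision in the primary estimate, and how far that estimate moves with whatever imbalance happens to occur.

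**Working it through.** **1. The plan's own sample size.** Inputs: difference 19 mm, SD 28 mm, two-sided α 0.05, power 80%, attrition 10%.

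n per arm = 2 × (28 × (1.960 + 0.842) / 19)² = 34.1, so 35. Then 35 / 0.9 = 38.9, so 39. The stated 40 is within rounding. With 40 × 0.9 = 36 evaluable per arm, noncentral-t power is 0.810. The sample size is not in question.

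**2. Formulas.** Let sx be the baseline SD, sy the week-4 SD and ρ their correlation.

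- Var(change) = sx² + sy² − 2ρ·sx·sy
- Var(adjusted) = sy²(1 − ρ²)
- Slope of week 4 on baseline = ρ·sy/sx

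**3. Assumptions.** The documents give neither ρ nor sx, and do not say whether 28 mm is the SD of the score or of the change. The entry rule confines baseline to 50–100 mm. A score on that range cannot have an SD above 25 mm, and an even spread gives 50/√12 = 14.4 mm. I therefore take sx 12–16 mm, sy 25–28 mm and ρ 0.2–0.5.

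**4. Variance and power.** Each variance ratio is applied to a change SD of 28 mm; power is noncentral t at 36 per arm for 19 mm.

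| sx | sy | ρ | Slope | Var(change) | Var(adjusted) | Ratio | Power after adjustment |
|---|---|---|---|---|---|---|---|
| 16 | 25 | 0.2 | 0.31 | 721.0 | 600.0 | 0.83 | 0.88 |
| 14 | 28 | 0.2 | 0.40 | 823.2 | 752.6 | 0.91 | 0.84 |
| 14 | 28 | 0.3 | 0.60 | 744.8 | 713.4 | 0.96 | 0.83 |
| 14 | 28 | 0.5 | 1.00 | 588.0 | 588.0 | 1.00 | 0.81 |
| 12 | 28 | 0.5 | 1.17 | 592.0 | 588.0 | 0.99 | 0.81 |

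Over the whole range the ratio runs from 0.83 to 1.00. That is a saving of about 0–17%, with power 81–88% against 81% unadjusted. Over a grid of sx 12, 14, 16; sy 25, 28; and ρ 0.2, 0.3, 0.4, 0.5, the slope is below 1 in 21 of 24 combinations, exactly 1 in one, and slightly above 1 in two.

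**5. Chance imbalance.** With sx = 14 and 40 per arm, the standard error of the baseline difference is 14 × √(2/40) = 3.1 mm. The part left in the change-score contrast is (1 − slope) × 3.1 mm. With sy = 28 this is:

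- ρ = 0.2: 0.6 × 3.13 = 1.9 mm
- ρ = 0.3: 0.4 × 3.13 = 1.3 mm
- ρ = 0.4: 0.2 × 3.13 = 0.6 mm
- ρ = 0.5: 0 mm

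For scale, the standard error of the treatment contrast is 28 × √(2/36) = 6.6 mm. The largest of these shifts is therefore just under 0.3 of a standard error, and 1.9/19 = 10% of the target difference.

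**The case against.** The strongest defence is that nothing in the planned test is invalid. Under 1:1 randomization a t test on change scores is unbiased over randomizations and keeps its type I error. The endpoint is defined as a change, the sample size was set for an unadjusted comparison of two means, and 40 per arm reproduces. The noise from baseline imbalance is already reflected in the test and its interval. All of this stands, and it limits the point to efficiency and to bias conditional on the imbalance that occurs.

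A second defence is the additional mixed model, whose terms a condensed article may leave to an analysis plan that is not shown. This stands in part: leaving out the terms is no fault. But the article does fix the test for the primary outcome, and the mixed model is only an addition to it.

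Two stronger readings are tempting and fail.

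- A reader might use the equal-SD result, in which adjustment leaves (1 + ρ)/2 of the variance, and infer savings of 35%, 25% or 15% at ρ = 0.3, 0.5 or 0.7, with a large rise in power. With a change SD of 28 mm this needs a baseline SD of 28/√(2(1 − ρ)) = 23.7, 28.0 or 36.1 mm. The last two exceed the 25 mm maximum that the entry rule allows, and the first needs nearly everyone at one end or the other of 50–100 mm.
- A reader might infer that change scores always over-correct an imbalance. They do so only when the slope is below 1.

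**Conclusion.** The point holds as a modest, free improvement and not as an error. The primary between-group test leaves out a covariate that is already collected. It is never more precise in large samples than the adjusted model, and it leaves part of a chance baseline imbalance in the estimate unless the slope is exactly 1.

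The gain may be close to nil, notably when ρ is near 0.5 and week-4 scores are about twice as spread as baseline scores. The top of the power range comes from the most favourable corner (baseline SD 16, week-4 SD 25, ρ = 0.2). The size rests on the assumed SDs and correlations, on reading 28 mm as the SD of change, on about 36 evaluable per arm, and on large-sample variance formulas that ignore the one degree of freedom spent on the slope.

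**What to change.** Before outcome data are analysed, restate the primary analysis as a linear model of week-4 first-step VAS (or of its change, which gives the same treatment effect) on arm and baseline VAS, reporting the adjusted mean difference with its 95% confidence interval. An acceptable alternative is the mixed model already planned, fitted to weeks 2 and 4 with baseline VAS as a covariate, with the week-4 contrast as the primary result. Name one of the two as primary.

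Use the same form for week-2 VAS and for the FFI subscales and total, each with its own baseline. Keep the unadjusted two-sample test as a sensitivity analysis.

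The cost is a change of wording in the analysis section. It needs no new data, visits or patients, and 40 per arm can stay.

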### Study monitoring

A dedicated team from the Hospital Authority Chinese Medicine Department (HACMD) that is completely uninvolved in the running of the study and has no competing interests will be responsible for monitoring the study progress. Pre-trial and post-trial onsite inspections and quarterly monitoring meetings will be held to oversee the progress of the study and ensure it is conducted, recorded, and reported in accordance with the protocol, Good Clinical Practice guidelines, and applicable regulatory requirements. Although a separate data monitoring committee will not be established, the HACMD will serve this function to ensure scientific validity, scientific integrity, and data accuracy through the regular monitoring of this clinical trial.

### Ethical considerations and dissemination of information

The study will be conducted in compliance with local laws. It will adhere to the common guidelines of the Declaration of Helsinki for medical research involving humans [59, 60] and the International Council for Harmonisation of Technical Requirements for Pharmaceuticals for Human Use–Good Clinical Practice (ICH-GCP) [61]. Ethical approval was obtained before the commencement of the study. The ethical validity of the study was approved by the Joint Chinese University of Hong Kong–New Territories East Cluster Clinical Research Ethics Review Committee (CREC Ref. No. 2017.600-T). Any modifications to the protocol are reported to this committee, and amendment approval should be obtained before any changes can take place. The study has been registered in the Chinese Clinical Trials Registry (ChiCTR1800014906). All individuals will receive sufficient information about the study, and written informed consent will be obtained from each person before enrollment. We plan to publish the results of this study in peer-reviewed journals or academic conference proceedings.

## Discussion

Patients who experience heel pain often suffer from pain and functional limitations. The prevalence of disabling foot pain will increase as the population ages. Acupuncture and moxibustion have been used to treat pain and functional limitations of heel pain for many years with positive results. Several previous studies have shown the positive therapeutic effects of electroacupuncture [23], warm needling [24], or the combination of both [25] for heel pain. According to these studies, single or combination therapy decreased pain intensity and symptoms of pain in patients with heel pain. However, because of the limitations of the study methodologies, little scientific evidence exists supporting the effectiveness of the methods. Therefore, we designed our study with an adequate methodology that follows international guidelines and uses validated assessment tools.

The objective of treating heel pain is to improve the quality of life by providing pain relief and preserving a patient’s foot function. The present study is an open-label, two-armed, parallel-group, randomized controlled trial that is designed to investigate the efficacy and safety of the combination therapy of electroacupuncture plus warm needling for treating patients with heel pain.

One limitation of the study is the possibility of a high risk of bias with regard to blinding because we used a waiting list as the control instead of a sham procedure. Owing to the nature of the acupuncture and moxibustion interventions, neither the study participants nor the acupuncturists can be blinded to the allocation and treatment stages.

This rigorously designed evidence-based clinical trial will evaluate whether electroacupuncture plus warm needling therapy is efficacious and safe in relieving pain and improving foot function among older adults with heel pain in Hong Kong. The present protocol may demonstrate electroacupuncture plus warm needling therapy as an effective and safe treatment option for patients with heel pain. The results obtained in the proposed study will provide valuable information and a solid foundation for future larger-scale clinical studies on the same topic. The study will provide evidence to determine whether the treatment protocol, which involves the combination of acupuncture and moxibustion, could be a potentially effective treatment alternative for heel pain.

## Trial status

The study commenced after receiving ethical approval. Participant recruitment began on 1 May 2018 and is expected to be completed on before 31 August 2019. This is version 4 of the protocol, dated 19 September 2018.

## Data Availability

The datasets used and/or analyzed during the current study will be available from the corresponding author after the completion of the study upon reasonable request.

## Abbreviations

BMI: Body mass index
CONSORT: Consolidated Standards of Reporting Trials
FFI: Foot Function Index
GRC: Global Rating of Change
HACMD: Hospital Authority Chinese Medicine Department
ICH-GCP: International Council for Harmonisation of Technical Requirements for Pharmaceuticals for Human Use–Good Clinical Practice
RCMP: Registered Chinese Medicine Practitioner
SPIRIT: Standard Protocol Items: Recommendations for Interventional Trials
STRICTA: STandards for Reporting Interventions in Clinical Trials of Acupuncture
STRICTOM: STandards for Reporting Interventions in Clinical Trials of Moxibustion
VAS: Visual analog scale
